### Study population

Approximately 516 tobacco smoking employees, randomized from 22 intervention companies and 22 control companies, participate in this study. To be eligible for participating in the study, companies have to meet certain criteria: (1) the management is willing to pay for the counseling sessions and (2) the management agrees that employees participate in the counseling sessions and carbon monoxide (CO) measurements during working hours or directly after on a location arranged by the company. In order to be eligible to participate in this study, an employee needs to be a current tobacco smoker and at least 18 years old. At the request of the employer, spouses who smoke are allowed to enroll in the study. Subjects are not eligible for participation in this study when they have an acute life-threatening disease, are not able to read or speak the Dutch language, or have already started an attempt to quit smoking at the moment of inclusion.

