### Intervention

#### Smoking cessation counseling

Evidence-based smoking cessation counseling is provided by experienced trainers of SineFuma to both employees in the intervention companies and the control companies. Groups of approximately 8–16 participants receive counseling in seven sessions of ninety minutes on a location arranged by the company. The training is practical in nature and focuses on ways to quit successfully and how to avoid relapse. It relies on a buddy system group dynamic to effectively promote peer support. The trainer informs participants about the possibility to use smoking cessation aids like nicotine replacement therapy and medication during their quit attempt. The company decides whether it reimburses the medication or if their employees have to claim it from their health insurance. After two sessions in which the participants are prepared, they stop smoking at the third session. In session four to seven, the participants receive counseling to get through the first difficult weeks of smoking abstinence. As a standard part of the smoking cessation training, participants perform a CO measurement every week starting the second session, which serves as a tool to motivate and encourage them to stay quit.

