### Randomization

Participants are allocated via cluster-randomization on a company level to the intervention or control group. For large corporations with several branches in which the participants are not in direct contact with each other, each location is entered separately in the randomization. The randomization procedure is performed by an independent research assistant. The sequence of the randomization is generated with a digital randomization program using the biased urn method [33, 34], where the proportion of being randomized into a group is inversely related with the proportion of participants who are already randomised into that group, in order to maintain treatment balance throughout the trial.

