### Statistical analysis

Based on the intention-to-treat principle, all randomized participants are included in the denominator for calculating abstinence rates with the exception of unavoidable loss to follow-up as stated the Russel Standard [29]. The primary effectiveness analysis examines the difference in prolonged smoking abstinence between intervention group and control group over a period of twelve months after the counseling sessions. To be able to account for repeated measures and nesting of participants within companies, generalized mixed models with the logit link are used. Time, group (intervention or control) and the interaction between time and group are entered in the model as fixed factors. Baseline measurements such as socioeconomic status (based on income and education) and nicotine dependence are considered as potential effect modifiers, and will therefore be explored by moderation in the analysis. If those are indeed effect-modifiers, the effects for each level of socioeconomic status and nicotine dependence are reported. In case of missing values in these potential effect modifiers, multiple imputation approach is used. Missing data in the outcome variable are not being imputed, since the likelihood-based approach is used to deal with missing values [35]. A two-tailed test is considered statistically significant with p-values <0.05.

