### Economic evaluation

An economic evaluation in the form of a cost-effectiveness (CEA) and cost-utility analysis (CUA) from a societal perspective and from an employer’s perspective [36] is embedded in this trial-based economic evaluation. The time horizon and the measurement point are combined with the effectiveness study, i.e. the T0-T4 measurement. The primary outcome for the CEA is cost per continuously abstinent ex-smoker. The primary outcome of the CUA is cost per Quality Adjusted Life Year (QALYs). The utility value derived from the standard quality of life questionnaire, EuroQol 5D5L [37], using Dutch tariff [38] will be used to compute QALYs. The utilities at the various time points are used to compute QALYs by means of the area under the curve method [39].

As this economic evaluation is also performed from a societal perspective, this implies that all relevant costs and outcomes are taken into account. A separate analysis is performed from the employer’s perspective. It is hypothesized that the intervention is associated with an increased number of quitters, increase in quality of life, and decreased costs. The time horizon is 12 months. Costs (the use of resources) are measured continuously; outcomes for the economic evaluation study are measured before the start of the smoking cessation training, at 3 months, 6 months, and 12 months.

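### The primary model uses baseline nicotine dependence and socioeconomic status only to explore moderation, so the main effect in 44 companies, randomised without described stratification, is not adjusted for either

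*Protocol article*

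**What the plan says.** The Statistical analysis section specifies that "generalized mixed models with the logit link are used", with participants nested in companies. It then lists the model terms: "Time, group (intervention or control) and the interaction between time and group are entered in the model as fixed factors". Baseline variables come in through the next sentence: "Baseline measurements such as socioeconomic status (based on income and education) and nicotine dependence are considered as potential effect modifiers". Their only stated consequence is that "If those are indeed effect-modifiers, the effects for each level of socioeconomic status and nicotine dependence are reported". Multiple imputation is planned for missing values in these variables.

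The Questionnaires section collects nicotine dependence and demographics at T0, before the training. Under Strengths and limitations the article says that smokers of low socioeconomic status (SES) are less likely to succeed in quitting.

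On the design, "Approximately 516 tobacco smoking employees, randomized from 22 intervention companies and 22 control companies, participate in this study". The Randomization section describes a biased urn in which "the proportion of being randomized into a group is inversely related with the proportion of participants who are already randomised into that group". This balances numbers; no stratification or balancing on covariates is described. Strengths and limitations concedes that, where groups at one location start at different times, employees in a later group may find out their condition before joining, and that this could cause selection bias. The same section expects a known incentive to attract occasional smokers, and a known control condition to attract heavy smokers.

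**The concern.** The two baseline variables that the authors single out enter only an exploratory analysis. A moderation model would normally carry their main effects, but the headline comparison, as the fixed factors are listed, does not.

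Three features make this worth changing. First, only 44 units are randomised, so baseline differences between arms are larger than under individual randomisation of the same number of people. Second, nothing in the described allocation balances dependence or SES. Third, the article names a route by which the arms could differ on smoking intensity for reasons other than chance. The standard error of an unadjusted model does not cover imbalance of that last kind. At stake are some precision in the primary result and some protection against, and credibility under, an imbalance seen at baseline. The validity of the trial is not in question.

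**Working it through.** **The plan's own figures.** Inputs from the Sample size calculation section: 15% against 5% abstinent, alpha 0.05, power 80%, 12 participants per company, ICC 0.05, 15% loss.

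- Two-proportion chi-square formula without continuity correction: 141 per group, as stated.
- Design effect 1 + 11 × 0.05 = 1.55; 141 × 1.55 = 218.55, so 219 per group, as stated.
- 219 / 0.85 = 257.6, so 258 per group and 516 in total; 516 / 12 = 43 companies, made even at 44.

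The sample size reproduces. The point rests on no arithmetic error, and the fix does not change the number of participants.

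**Chance imbalance in an individual-level baseline score.** With 258 per arm in clusters of 12, the SD of the between-arm difference, in units of the score's own SD, is sqrt(2/258 × (1 + 11 × ICC)). The ICC of the score is not in the article; 0 to 0.20 is assumed.

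| Score ICC (assumed) | SD of difference | 1.96 × SD |
|---|---|---|
| 0 | 0.088 | 0.173 |
| 0.05 | 0.110 | 0.215 |
| 0.10 | 0.128 | 0.250 |
| 0.20 | 0.157 | 0.309 |

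**Effect on the treatment odds ratio.** Design odds ratio: (0.15/0.85) / (0.05/0.95) = 3.35. If the score has odds ratio R per SD, an imbalance of d multiplies the treatment odds ratio by about exp(d × ln R). R is assumed to lie between 1.3 and 2.0.

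- R = 1.3, ICC 0.05, d = 0.215: factor 1.06.
- R = 2.0, ICC 0.10, d = 0.250: factor 1.19.

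An imbalance at the 1.96 limit would therefore move 3.35 up to between 3.55 and 3.99, or down to between 3.16 and 2.82.

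**Share of the existing uncertainty.** With the effective 141 per group, which already carries the design effect, the variance of the log odds ratio is about 1/(141 × 0.15 × 0.85) + 1/(141 × 0.05 × 0.95) = 0.0556 + 0.1493 = 0.205, giving a standard error of 0.45. Chance imbalance on the score contributes an SD of 0.110 × ln 1.3 = 0.029 up to 0.128 × ln 2.0 = 0.089. As a share of variance this is 0.029² / 0.205 = 0.4% up to 0.089² / 0.205 = 3.9%. It is a small part of an uncertainty that the unadjusted analysis already reports.

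**Room for extra terms.** Expected participants abstinent at 12 months: 219 × 0.15 + 219 × 0.05 = 32.9 + 11.0, or about 44.

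**Imbalance that is not chance.** The article does not say how many companies will run later groups, so this part cannot be sized. Its direction follows from the article's own account: lighter smokers in incentive companies and heavier smokers in control companies. Dependence at T0 is the collected variable closest to that mechanism.

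**The case against.** The best case for the plan is that it contains no error. Under randomisation, a cluster-aware unadjusted model is valid, and chance imbalance is part of its standard error; the design effect of 1.55 already pays for variation between companies. Adjustment is then a preference about precision, and covariate lists are often left to an analysis plan. Much of this stands. A reader might infer that chance imbalance biases the primary effect; it does not. What does not stand is that the model was left open: the article lists the fixed factors and gives these two variables a different role. The argument also does not cover the selection of later groups, which the authors themselves raise.

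Adjustment has its own costs. About 44 primary events do not support a long covariate list, and the adjusted odds ratio is conditional on the covariates. Both are fair and both are manageable.

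Two wider readings are tempting.

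- **Medication reimbursement as a covariate.** The Smoking cessation counseling section says "The company decides whether it reimburses the medication or if their employees have to claim it from their health insurance", and the Background says that full reimbursement of therapy can double long-term quitting. That doubling runs through more smokers taking up therapy. Here everyone has enrolled, and every company pays for the counselling. The contrast is who pays for medication, its effect is not given, and the policy is not listed as collected.
- **An unadjusted economic analysis.** The Economic evaluation section says "The utilities at the various time points are used to compute QALYs by means of the area under the curve method". That describes how each person's QALY is built and does not exclude regression on T0 utility. The article is silent on adjustment for T0 utility or costs, which a condensed article may leave to a fuller document. With utilities at 0, 3, 6 and 12 months, T0 carries an area weight of only 0.25 / 2 = 0.125.

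**Conclusion.** The point holds as a modest, specific improvement to the primary model. The main effect, as specified, is not adjusted for two baseline variables that the authors themselves single out. For SES the article gives its own evidence of prognostic value; for nicotine dependence it gives no strength. The unadjusted analysis remains valid.

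Under the assumed prognostic strengths and score ICCs, chance imbalance accounts for roughly 0.4% to 4% of the variance of the log odds ratio, and an imbalance at the 1.96 limit shifts the odds ratio by about 6% to 19%. No power gain can be derived from the document, because the variance explained by the covariates is not given. The stronger reason to adjust is the conceded risk of informed enrolment in later groups. Adjustment would be only partial protection there, since motivation and other unmeasured differences would remain. If an existing analysis plan already makes the adjusted model primary, only the wording of the article needs to be aligned.

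**What to change.** In the Statistical analysis section:

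1. Add nicotine dependence and SES as pre-specified main-effect covariates in the primary mixed model, alongside time, group and their interaction. Use T0 values only, because dependence is asked again at every later measurement and those values can be affected by treatment.
2. Fix the coding in advance. One score for each variable keeps the addition to two terms; each further SES category would use another.
3. Use the multiple imputation already planned for missing values of these two variables.
4. Keep the moderation tests as exploratory analyses, separate from the primary estimate.
5. State that the odds ratio is conditional on the covariates, as it already is on company through the mixed model, or also report a standardised risk difference. Give the unadjusted result as a sensitivity analysis.

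The cost is a change of model wording, two extra terms against about 44 expected primary events, and a conditional estimand to explain. No extra participants or data collection are needed.

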### Sample size calculation

The study from Volpp et al. [18] is used to obtain estimates for the sample size calculation. After 12 months, 15 % of participants in the intervention group and 5 % in the control group were abstinent. With an alpha of 0.05, the required sample size to obtain this clinically relevant effect size with 80 % power is 141 participants per treatment group, based on the Chi-square test.

Since the randomization is on cluster (company) level and assuming a mean number of participants per company (m) of 12 and an intra-class correlation (ICC) of 0.05 [31], the design effect 1 + (m-1) ICC = 1.55, yields a sample size of 219 participants per group. Taking into account 15 % loss to follow up due to unexpected employee turnover [18], 516 participants (44 companies) have to be included in the study in total.

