### Strengths and limitations

The proposed study has several strengths, starting with its company setting. A company setting can have several advantages compared to other settings; corporations have the potential to reach a large amount of people, can motivate their employees to participate and thereby achieve high attendance rates, and may inspire peer support and positive peer pressure among colleagues [46]. Moreover, businesses have an interest in keeping their employees healthy [4].

Another strong point of this study is that the proposed study performs a cost-effectiveness and cost-utility analysis from a societal perspective and specifically from an employer’s perspective. To our best knowledge, the cost-effectiveness of financial incentives to stimulate long term smoking cessation in a company setting has not been established yet. The outcomes of the cost-effectiveness analysis can help inform employers who are considering providing smoking cessation support in combination with incentives for their employees.

What makes this study also particularly relevant is its target population of employees with a lower socioeconomic status. People with a lower education and income smoke more often [25, 47], smoke more cigarettes per day and have lower quit rates than people with a higher SES [26, 48]. Although smokers with low SES are as likely to start a quit attempt as smokers with a high SES, they are less likely to succeed in quitting smoking [49]. Potential barriers in quitting successfully are suggested to be lack of social support and financial barriers to smoking cessation treatment [47]. The current intervention aims to remove potential obstacles and to make the smoking cessation program easily accessible for employees in three ways: (1) by providing it via the employer, (2) by organizing the training sessions at the workplace, and (3) by designing the training as a group program so that colleagues can support each other both during and between sessions.

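### Effects by socioeconomic status and nicotine dependence are to be reported if effect modification is found, but the trial is sized only for the main effect, so they would usually go unshown and, when shown, the contrast between levels would be overstated

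*Protocol article*

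**What the plan says.** In the protocol article, the Statistical analysis section says that baseline measurements such as SES and nicotine dependence "are considered as potential effect modifiers, and will therefore be explored by moderation in the analysis". The next sentence sets the reporting rule: "If those are indeed effect-modifiers, the effects for each level of socioeconomic status and nicotine dependence are reported". The only decision criterion in the section is a general one: "A two-tailed test is considered statistically significant with p-values <0.05". No separate level is given for the moderation tests, and no sentence says that level-specific effects will be shown if modification is not found.

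The Sample size calculation section powers the overall comparison only. It assumes that "15 % of participants in the intervention group and 5 % in the control group were abstinent" and arrives at "141 participants per treatment group, based on the Chi-square test", then adjusts for clustering and loss to follow-up. No power is given for effect modification.

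The Strengths and limitations section says: "What makes this study also particularly relevant is its target population of employees with a lower socioeconomic status".

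**The concern.** The rule makes what is published depend on what is found. Two consequences follow if the interaction test has low power.

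First, real differences between SES levels would mostly be missed, and the level-specific estimates would then not be shown. A reader could take the silence as evidence of equal benefit across levels, which a weak test cannot support.

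Second, a weak test is passed mainly by samples in which the contrast happens to be large. The level-specific effects that do get published would therefore show too large a difference between levels.

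This matters more than for an incidental subgroup, because lower-SES employees are put forward as a main reason for the trial. It is a rule that the article states, not a detail left to an analysis plan.

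**Working it through.** **Reproducing the plan's figure.** Inputs from the Sample size calculation section: 15% vs 5%, two-sided alpha 0.05, 80% power, 12 participants per company, ICC 0.05, 15% loss.

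- n per arm = [1.96·√(2·0.10·0.90) + 0.84·√(0.15·0.85 + 0.05·0.95)]² / 0.10² = 140.1, rounded up to 141.
- Design effect = 1 + 11·0.05 = 1.55; 141·1.55 = 218.55, so 219 per arm.
- 219/0.85 = 257.6, so 258 per arm and 516 in total.

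The stated numbers are reproduced. They give 80% power for the overall effect, whose planned odds ratio is (0.15/0.85)/(0.05/0.95) = 3.35.

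**Assumptions for the interaction.** The article gives no SES split, number of levels or stratum-specific rates, so what follows is illustrative.

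- Two equal strata and 219 evaluable per arm give 219/2 = 109.5 per cell with design effect 1.0, and 109.5/1.55 = 70.6 with design effect 1.55.
- The contrast is the log of the ratio of odds ratios at 12 months, because the planned model uses a logit link. This simplifies the planned repeated-measures mixed model.
- Variance = sum over the four cells of 1/[n·p·(1−p)].
- Power = Φ(d/se − 1.96) + Φ(−d/se − 1.96), where d is the true contrast.

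**Scenario A: 5→20% in one stratum, 5→10% in the other.**

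- Odds ratios 4.75 and 2.11; ratio 2.25; d = 0.811.
- Design effect 1.0: variance = 0.1923 + 0.0571 + 0.1923 + 0.1015 = 0.543; se = 0.737; d/se = 1.10; power 20%.
- Design effect 1.55: se = 0.737·√1.55 = 0.917; d/se = 0.88; power 14%.
- Simulated binomial cells of 110 or 71, with 0.5 added to each count, give 18% and 12%.
- Range 12–20%, so level effects are unshown in about 80–88% of such trials.

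**Scenario B: 5→15% in one stratum, 5→5% in the other.**

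- d = ln 3.35 = 1.210.
- Design effect 1.0: variance = 3·0.1923 + 0.0716 = 0.649; se = 0.805; power 32%.
- Design effect 1.55: se = 1.003; power 23%.
- The same simulation gives 30% and 18%.
- Range about 18–32%, so level effects are unshown in about 68–82%.

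**What would be needed.** With 5% vs 15% in both strata as the base for the variance, se = √[2·(0.1923 + 0.0716)] = 0.726. The ratio of odds ratios detectable with 80% power is exp(2.80·0.726) ≈ 7.7 with design effect 1.0, and exp(2.80·0.726·√1.55) ≈ 12.6 with 1.55. The planned main effect is 3.35.

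**Where the conclusion weakens.** For 5→25% vs 5→5%, power is 47–65% by the formula. The Background section also gives higher quit rates among programme participants in the cited employee trial (46.3% vs 20.8%). At about those rates, 21→46% vs 21→33% gives only 17–24%, while 21→46% vs 21→21% gives 55–74%.

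**Overstatement after selection.** In scenario A the mean absolute contrast among significant results, divided by the true contrast, is 2.28 and 2.79 by the normal approximation, and 2.3 and 2.9 in the simulation. In scenario B, by the normal approximation, it is 1.7 and 2.1.

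**Effect on the low-SES estimate itself** (scenario A, design effect 1.55):

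- If low SES is the stratum that benefits more, its true log odds ratio of 1.56 averages 2.20 among significant results.
- If low SES benefits less, its true 0.75 averages about 0.

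**The case against.** The strongest reply has five parts.

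- **The text does not say that level effects are withheld otherwise.** This is true of the literal words. But the condition would serve no purpose if the effects were shown anyway, so the restrictive reading is the natural one. The p<0.05 gate is likewise inferred from the general sentence on significance. Nor does the article say that the interaction estimate itself goes unreported.
- **The low-SES group is not left without a result.** The overall effect is always reported, and the Recruitment section prefers companies with lower-educated workers. A reader might infer that the trial will say nothing about this group; that goes too far. Eligibility is not restricted by SES, however, so the overall effect stands in for it only in part.
- **The numbers rest on undocumented inputs.** This stands, and the figures are illustrative. The design effect of 1.55 is an upper bound to the extent that SES varies within companies. A continuous SES score would gain some power. On the risk-difference scale, over equal and 70/30 splits, power would be higher: about 28–43% for 5→20% vs 5→10%. The planned model works on the logit scale. Nothing specific to nicotine dependence was computed; the same arithmetic applies to any two-level split with these rates.
- **Testing the interaction first guards against over-reading noisy subgroups.** It is a common practice with a reasonable motive. Labelling and confidence intervals meet that motive without making reporting depend on the result.
- **Always reporting does not create power.** Correct. At 5% vs 15% the 95% interval for one stratum has half-width 1.96·√(0.175/n), which is 7.8 points with n = 109.5 and 9.8 points with n = 70.6, around a planned effect of 10 points.

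A reader might also infer that the rule exaggerates the low-SES effect. It does not do so in a known direction: what is inflated is the difference between strata.

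**Conclusion.** The point holds as a minor, inexpensive improvement to a stated reporting rule. On the natural reading of that rule, and with two equal SES strata, 219 evaluable per arm and a design effect of 1.0 to 1.55, the gatekeeping test has roughly 12–32% power across the two main scenarios. It passes 50% only for extreme contrasts under favourable assumptions. Level-specific estimates would usually not be shown. When shown, the difference between strata would be overstated on average, about 2.3–2.9 times for 5→20% vs 5→10%, and the low-SES effect could be distorted in either direction. If there is no true modification, the estimates go unshown in 95% of trials.

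The documents do not support a stronger conclusion. The analysis is labelled exploratory, and the primary comparison and the sample size are untouched.

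**What to change.** Replace the conditional sentence in the Statistical analysis section. State that the group-by-SES and group-by-nicotine-dependence interaction estimates, and the difference in abstinence between arms within each level, will be reported with 95% confidence intervals whatever the p-value and labelled exploratory. State also that the overall arm effect remains the primary result in all cases.

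The cost is one extra table or forest plot from the same models and data. The drawback is that the intervals will be wide, so the text should warn against reading differences between levels as established.
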